### *The practical procedures, studies, and outcomes*

The 400 patients are recruited at the involved surgical departments:

- Herlev Hospital ([name]),
- Regionshospitalet Horsens ([name]),
- Sjællands Universitetshospital Køge ([name]),
- Sjællands Regionshospital Holbæk ([name]).
- - more departments – also in the private sector – may be included if necessary and after extended approval from the Ethical Scientific Committee and the Danish Data Protection Agency.

Standard protocol for SNAP at Horsens: Weight loss information and smoking cessation as BMI < 30 and smoking cessation (without verification by urine cotinine test) are mandatory.

Standard protocol for SNAP at Zealand University Hospital, Køge: Weight loss information, smoking cessation - active surveillance, and follow-up by nurses aiming at BMI < 35 and smoking cessation (without verification by urine cotinine test) mandatory.

Standard protocol Herlev University Hospital: The aim is a general optimization prior to surgery, including regarding BMI and smoking (without verification by urine cotinine test).

Standard protocol Zealand Regional Hospital, Holbæk: The aim is a BMI under 35 and optimization of any comorbidity prior to surgery. For operation of major hernia of 10 cm or more, it is recommended to stop smoking six weeks preoperatively (without verification by urine cotinine test).

After informed consent, patients are included and allocated to either the 6-week STRONG intervention or the control group. Data collection takes place at baseline, after 6 weeks/at time of surgery, and postoperatively after 1, 3 and 6 months at the local surgical department. The data are included in the databank in Redcap, and blood and urine samples are transferred to the established project biobank at the Parker Institute. For the long-term follow-up on health, further data are drawn from national health registries up to 2-years after the inclusion (project flow in figure 1).

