### Outcomes and data collection (Table 1)

Postoperative complications (within 1, 3, 6 months after surgery): The primary outcome is the number of patients with > 1 complication, defined by requiring documented treatment, categorized in accordance with the Clavien-Dindo grading and the Comprehensive Complication Index (CCI). They include adverse events and side effects. Secondly, length of stay, second surgery, revisits and – admissions at hospital, visits in primary care, time back to work or previous activities.

Successful risk reduction at follow-up/at surgery: Defined as SNAP below risk level validated as described in chapter 2; for obesity BMI < 30 or at least 5% and max 10% loss of body fat mass preoperatively (0.5–1 kg/weekly without developing malnutrition). Data are collected via logbook and validation.

For frailty: In addition to pI-protein, the frailty level (0-5, 0 is best) is measured by Fried's Modified Frailty Score according to Blammers as that is associated with development of complications. It includes five criteria:

- Slowness: Performance time in the walking test,
- Weakness: Hand grip strength measured by a dynamometer,
- Exhaustion: Responding "All the time" or "Often" to the item "I feel everything is an effort / I can't get going" in the Hospital Anxiety & Depression Scale.
- Weight loss: Self-reported 5 kg over the last year
- Low activity: Below 3 MET

Health (at baseline, after 6 weeks/at surgery, and 6 months postoperatively): This is measured by the health-related quality of life measured by EQ-5D with 5 dimensions and the overall health measured with a scale from 0 to 100 with a higher score representing a better health. Within 2 years of follow-up, the morbidity is measured as visits and stay at hospital as well as visits in primary care and prescribed medicine and grouped diagnoses groups as well as mortality.

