| Revisits and readmissions at hospital                                                                 |           |                        | X                    | X                       |
| Visits in primary care                                                                                |           |                        | X                    | X                       |
| Long-term register data on Health and Costs                                                    |           |                        | Up to 2 years |                         |
| Morbidity (National patient registry)                                                                 |           |                        |                      | X                       |
| Mortality (Death certificate registry)                                                                |           |                        |                      | X                       |
| Individual DRG costs at hospital (DRG registry)                                                       |           |                        |                      | X                       |
| Primary care usage (Primary care registry)                                                            |           |                        |                      | X                       |
| Prescribed medicine (Medicine registry)                                                               |           |                        |                      | X                       |

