### 3c. Interventions

Intervention group: Patients in the intervention group receive minimum five educational sessions over 6 weeks (i.e., about weekly) as an integrated prehabilitation program tailored to meet the

individual patient's need for risk reduction at surgery, see Table 2 and 3. It is introduced via the surgical 'Engage in the process of change'. The smoking intervention follows the Gold Standard Programme GSP, which has been translated to the standardized alcohol cessation intervention, exercise training programme, and nutritional intervention.

Project nurses from the participating centre, who have taken part in a 5-day educational program followed by practical training in the Gold Standard Programme (GSP), provide the intervention. The project leader ([name]) of the trial ensures that counsellor follows the principles of the GSP program by regular discussion of the intervention.

Table 2. Weekly sessions after inclusion (Preop: preoperatively)

|                                  | Week 1 | Week 2 | Week 3 | Week 4 | Week 5 | Week 6 Follow-up
+ continued preop. |
|----------------------------------|--------|--------|--------|--------|--------|----------------------------------------|
| Smoking cessation                | X      | X      | X      | X      | X      | X                                      |
| Nutrition program (malnutrition) | X      | X      | X      | X      | X      | X                                      |
| Nutrition program (obesity)      | X      | X      | X      | X      | X      | X                                      |
| Alcohol cessation                | X      | X      | X      | X      | X      | X                                      |
| Physical Activity                | X      | X      | X      | X      | X      | X                                      |

Table 3. The patient education program in the Gold Standard Programme (GSP)

| Week number                | Education subject                                              |
|----------------------------|----------------------------------------------------------------|
| 1 (at inclusion)           | Level of motivation, ambivalence, pros and cons (see Appendix) |
| 2                          | Dependence, withdrawal symptoms (experience and expectations)  |
| 3                          | Relapse (description and management)                           |

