| Weight and bio-impedance                          | X     | X      | X      | X      | X      | X       |
| Validation by Nutrition profile (blood)           | X     |        | X      |        | X      | X       |
| Physical Activity                          |       |        |        |        |        |         |
| Physical activity according to plan               | X     | X      | X      | X      | X      | X       |
| Steps walked per day                              | X     | X      | X      | X      | X      | X       |
| Walking test                                      | X     |        | X      |        | X      | X       |
| Hand grip strength                                | X     |        | X      |        | X      | X       |

Control group: All patients in the control group receive the project information about the study. They receive the routines of the involved departments (e.g., smokers may receive the Very Brief Advise and referral to a municipal clinic for smoking cessation intervention). All patients are free to use any support offered outside the project, including the free access to lifestyle intervention in their municipality.

All participants: All meetings are planned in connection with scheduled visits in the outpatient clinic or at admission to hospital when possible and in other cases the transportation for the weekly meetings will be reimbursed. All participants have telephone access to the research nurse during the project.

All receive routine procedures on general patient information, thromboembolic prophylaxis and antibiotics, anaesthesia, surgical intervention, and postoperative care as used at the centre. All patients are evaluated at inclusion and 6 weeks after/at surgery as well as 1, 3 and 6 months postoperatively, Table 1.

To find out if eligible patients who decline to participate in the trial differ from those enrolled, we ask for permission to follow them perioperatively via the medical records and for 2 years in the health registries. Those who accept are asked to provide informed consent.

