## STRONG – Hernia, Version 5 (12-05-2024)

All participants are included after informed consent and can withdraw their consent without further explanation and without influence on the treatment and care in the department. Patients, who withdraw the informed consent or say no thank you to participate in the randomised trial are asked about a separate informed consent for being followed-up via the medical records and the health registries.

The informed consent is collected timely to allow for 4-6 weeks prehabilitation with the STRONG program. If the operation is postponed, the prehabilitation period is extended until surgery (e.g., 8-

|                                              | 2023 | 2024 | 2025 | 2026 |
|----------------------------------------------|------|------|------|------|
| Protocol article writing                     | X    |      |      |      |
| Study 1-A Inclusion & data collection | X    | X    | X    |      |
| Analysing +Article writing                   | X    | X    |      |      |
| Study 1-B Data collection             | X    | X    | X    | X    |
| Analysing + Article writing                  |      | X    | X    | X    |
| Study 2 Data collection               |      | X    | X    | X    |
| Analysing + Article writing                  |      |      | X    | X    |
| Study 3 Data collection               |      | X    | X    | X    |
| Analysing + Article writing                  |      |      |      | X    |
| Study 4-A Analysing + Article writing |      |      | X    |      |
| Study 4-B Analysing + Article writing |      |      |      | X    |
| Study 4-C Analysing + Article writing |      | X    |      |      |
| Study 4-D Analysing + Article writing |      | X    |      |      |
| Running information of the project           | X    | X    | X    | X    |

12 weeks). They are also welcomed to use the project hotline in case of further questions and considerations. Participants are included only after informed consent and would then be randomized to either the intervention or control group.

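### The two-year morbidity count does not exclude STRONG sessions, so any session recorded as a separate hospital contact would score as morbidity in the intervention arm

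*Protocol*

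**What the plan says.** The Health paragraph of Outcomes and data collection (Table 1) defines long-term morbidity largely by service use: "the morbidity is measured as visits and stay at hospital as well as visits in primary care", with prescriptions, diagnosis groups and mortality added. Table 1 names the national patient registry as the source for morbidity. For the period covered, The practical procedures, studies, and outcomes says that "further data are drawn from national health registries up to 2-years after the inclusion". This outcome serves Study 2 in section 2a, the comparison of health gain at 6 months and 2 years.

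Section 3c describes what only one arm receives: "Patients in the intervention group receive minimum five educational sessions over 6 weeks". The sessions are run by nurses from the surgical centres. Section 12 adds: "If the operation is postponed, the prehabilitation period is extended until surgery". On attendance, section 3c plans meetings around scheduled outpatient visits or admission where possible, and "in other cases the transportation for the weekly meetings will be reimbursed".

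No section says whether STRONG sessions enter the registry as hospital contacts, or whether they are left out of the morbidity count.

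**The concern.** A visit count works as a measure of morbidity only if illness drives the visits. Here one arm is given extra attendances by the trial itself, apparently inside the counting window. Two patients with the same health could then receive different morbidity scores because one was allocated to STRONG.

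The error would run against the intervention. It could hide or reverse a real fall in healthcare use, which is part of what Study 2 sets out to detect. The sessions are a genuine use of resources and belong in the cost analysis. They are not a sign of ill health.

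**Working it through.** **Plan's own figure.** The protocol gives no figure for two-year morbidity. Its only sample-size figure is for the primary outcome (section 4: 20% against 10%, 80% power, two-sided 0.05). With pooled variance, n = [1.960·√(2·0.15·0.85) + 0.842·√(0.2·0.8 + 0.1·0.9)]² / 0.10² = (0.990 + 0.421)² / 0.01 ≈ 199 per arm, as stated. The present point does not touch it.

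**Can sessions be separate attendances?**
- Table 4, for the intervention group only, lists measurements at each weekly meeting, according to the patient's risk factors. They include breath tests and weighing, which need the patient present.
- Before surgery, Table 1 gives both arms a common evaluation only at inclusion and at week 6 or surgery. Sessions in weeks 2 to 5 have no counterpart in that schedule.
- Paying transport for meetings not tied to a scheduled visit shows that some separate attendances are expected. Their share is not stated.

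**Size.** Let *e* be the recorded extra visits per STRONG patient and *m* the control mean over two years. The relative excess is *e/m*. Neither quantity is in the protocol, so both are varied. The upper end for the core programme at its minimum is *e* = 5, or 200 × 5 = 1,000 visits across the arm.

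The planned test for continuous variables is Mann-Whitney at p < 0.05 (section 3a, Analyses). It was simulated with 200 per arm, negative binomial counts with dispersion 1 (variance *m* + *m*²), no true difference, and *e* added to every STRONG patient, in 1,000 runs per cell (standard error at most √(0.25/1000) ≈ 1.6 percentage points). Each cell shows the relative excess, then the share of trials rejecting.

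| Extra recorded visits | m = 5 | m = 10 | m = 20 |
|---|---|---|---|
| 0 | 0%; 5.0% | 0%; 6.1% | 0%; 5.1% |
| 1 | 20%; 83% | 10%; 36% | 5%; 13% |
| 2 | 40%; 100% | 20%; 84% | 10%; 35% |
| 3 | 60%; 100% | 30%; 99% | 15%; 64% |
| 5 | 100%; 100% | 50%; 100% | 25%; 96% |

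The zero row is the result once programme contacts are excluded: no artificial excess, and rejection near the nominal 5%.

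Masking follows by the same arithmetic. If STRONG truly cut a mean of 10 visits to 8, two recorded sessions would return it to 8 + 2 = 10.

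**The case against.** **Registration is not documented.** The sessions are a project activity, the grant covers project staff, and trial data go to REDCap. This stands. The bias is conditional, and it is nil if no session reaches the patient registry.

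**The start of the count is inferred.** The wording on registry data fixes where the draw ends, and Table 1 marks the register items under follow-up, a term its caption uses for postoperative time points. A postoperative count is therefore possible. But the only anchor the text gives is inclusion, and in an intention-to-treat comparison the natural window starts there.

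**This could be left to the analysis plan.** An analysis plan, not shown here, could define the exclusion. But the protocol itself chooses visits as the measure and ties the window to inclusion. As stated, the measure can differ by arm through allocation alone, which is more than missing detail.

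**Stronger readings a reader might infer, which the protocol does not support:**
- *That every session counts as illness.* Sessions are merged with scheduled visits where possible, so five extra visits is the upper end for the minimum programme. If surgery is postponed the programme continues, but no session frequency is given for that period, so no larger figure can be derived.
- *That STRONG's supportive medicines inflate the prescription count.* Section 3c says study medication is free to the patient and section 10 says the grant pays for it. Nothing shows it reaching the medicine registry.
- *That controls have no preoperative contacts.* Standard care includes nurse follow-up at Køge, and both arms attend the same scheduled evaluations. Only the STRONG sessions themselves are one-sided.
- *That the whole outcome is distorted.* A session as such does not inflate diagnosis groups or mortality.

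**Conclusion.** The point holds as a conditional bias in the visit component of one secondary outcome. The protocol measures two-year morbidity partly by hospital visits, its window on the natural reading includes a programme given to one arm, and nothing takes that programme out of the count.

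The conclusion rests on two assumptions: that the count starts at inclusion, and that some sessions are registered as separate hospital contacts. If so, the comparison is biased against STRONG, and one or two recorded visits per patient can matter: 36% and 84% rejection without any true difference at an assumed control mean of 10, and 13% and 35% at 20. These figures depend on the assumed means and dispersion and show the order of size only. The primary outcome and the sample size are not affected.

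**What to change.** Keep the randomisation-based window, identical for both arms, and add one sentence to the Health outcome definition, for example: *Registry contacts made solely for STRONG sessions or for study visits, identified by REDCap visit dates, are excluded from the two-year morbidity count in both arms and retained in the cost outcome; contacts combined with a scheduled clinical visit stay in the count.* State also that the count starts at inclusion.

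Counting from surgery would avoid most of the problem but should be a sensitivity analysis only. Surgery happens after randomisation, so if STRONG changes its timing or occurrence, observation time differs by arm. It would also drop genuine preoperative contacts, including any caused by side effects of the programme.

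The cost is the linkage of REDCap dates to registry contacts and possible misclassification of a few same-day contacts. The rule can be set before the registry data are drawn, and it needs no new data collection.

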## STRONG – Hernia, Version 5 (12-05-2024)

Prevalence of SNAP factors at baseline and the potential for risk reduction. Data are collected from the medical records. .

Costs (after 1 month, 6 months, and 2 years): Data on direct healthcare costs are collected for each individual patient from the National Hospital Costs Registry (DRG-registry) and the National Registry on Primary Healthcare. Data on cost-effectiveness includes the EQ-5D on Health outcome as described above.

Qualitative outcomes for the intervention group: The patient reflections and expectations regarding motivation, priority and self-efficacy for lifestyle changes are collected prior to the intervention. The information is measured at a scale from 0-100 (100 being the highest level). Free text is collected regarding the benefits and challenges of continuing and quitting the lifestyle.

*Table 1: Data collection for all included participants at baseline, after 6 weeks/surgery, and at follow-up 1, 3 and 6 months postoperatively, as well as after 2 years.*

| Measurements                                                                                          | Inclusion | Week 6 /
at surgery | Follow-up
30 days | Follow-up
3+6 months |
|-------------------------------------------------------------------------------------------------------|-----------|------------------------|----------------------|-------------------------|
| Socio-Demographic data (patient reported)                                                      |           |                        |                      |                         |
| Age and education (years), sex, housing, living alone, working conditions, level of daily activities  | X         |                        |                      |                         |
| SNAP Screening for risk: yes/no (patient reported)                                             |           |                        |                      |                         |
| Smoking, Nutrition, Alcohol, Physical activity                                                        | X         |                        |                      |                         |
| Status (patient reported)                                                                      |           |                        |                      |                         |
| Smoking (n° cigarettes/day, Nutrition (intake), Alcohol (n° drinks/week), Physical activity (min/day) | X         | X                      | X                    | X                       |
| EQ-5D (HRQoL)                                                                                         | X         | X                      | X                    | X                       |
| Adverse events                                                                                        |           | X                      | X                    | X                       |
| Status (validated)                                                                             |           |                        |                      |                         |
| Blood + urine: Alcohol & Nicotine biomarkers, Hgb, Albumin, Protein, ASAT, Bilirubin                  | X         | X                      | X                    | X                       |
| Weight and bio-impedance, height,                                                                     | X         | X                      | X                    | X                       |
| Frailty score (weight loss, handgrip, walking test, exhaustion, level of activity)    | X         | X                      | X                    | X                       |
| ASA-score                                                                                             | X         | X                      | X                    | X                       |
| Postoperative complications                                                                    |           |                        |                      |                         |
| Complications /yes/no)                                                                                |           |                        | X                    | X                       |
| Clavien-Dindo grade and CCI                                                                           |           |                        | X                    | X                       |
| Stay in hospital                                                                                      |           |                        | X                    | X                       |
| Second surgery                                                                                        |           |                        | X                    | X                       |
| Revisits and readmissions at hospital                                                                 |           |                        | X                    | X                       |
| Visits in primary care                                                                                |           |                        | X                    | X                       |
| Long-term register data on Health and Costs                                                    |           |                        | Up to 2 years |                         |
| Morbidity (National patient registry)                                                                 |           |                        |                      | X                       |
| Mortality (Death certificate registry)                                                                |           |                        |                      | X                       |
| Individual DRG costs at hospital (DRG registry)                                                       |           |                        |                      | X                       |
| Primary care usage (Primary care registry)                                                            |           |                        |                      | X                       |
| Prescribed medicine (Medicine registry)                                                               |           |                        |                      | X                       |

